## Methods and design

Visual-acoustic Intervention with Service delivery In-person and via Telepractice (VISIT) is a parallel-group prospective randomized controlled non-inferiority trial measuring the efficacy of visual-acoustic biofeedback intervention for RSSD affecting /ɹ/ when delivered online versus in-person. All participants will receive visual-acoustic biofeedback intervention following a standard protocol and schedule; they will be randomly assigned to receive this intervention either in the laboratory setting or via online telepractice. Participant allocation in each group will be stratified by pre-treatment severity, since previous research has identified this variable as an important indicator of subsequent treatment response. Finally, allocation will additionally be stratified by site (Montclair, New Jersey; Syracuse, New York). Although not all participants will be physically present at their allocated site during treatment delivery, they must reside close enough to their study site to be able to participate in-person if randomized to that condition. They will also interact with a site-specific study team, which could potentially be relevant for study outcomes.

We plan to enroll a total of 76 children with RSSD. The power analysis to determine this sample size was based on a comparison of 12 participants from a previous study who received visual-acoustic biofeedback treatment in the in-person setting and 11 participants who received a comparable duration of visual-acoustic biofeedback treatment via telepractice. The participants seen in person had an average change score of 39.8% points (standard deviation = 25.8% points) and the participants seen online had an average change score of 36.8% points (standard deviation = 22.6% points). The population standard deviation of the outcome, after controlling for effects of clinician and baseline accuracy, was estimated at 18% points. Using the formula from Flight & Julious 2016 [32], the sample size of 38 participants per group was computed to achieve 80% power for an alpha level of 5%, assuming the non-inferiority margin delta derived as described under *Data analysis plan*. Power analysis was conducted using an online power calculator for non-inferiority trials [33].

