### Group allocation

Participants will be randomly allocated to one of two groups in a 1:1 ratio. The *in-person* group will receive visual-acoustic biofeedback treatment from a clinician in a private room in research space at Syracuse University or Montclair State University, while the *telepractice* group will receive equivalent treatment delivered via videoconferencing. As indicated above, random allocation will be stratified by both baseline accuracy and study site. To determine baseline accuracy, the stimulability probe will be rated by the clinician who administered the evaluation and a clinician at the other study site. Based on these ratings, participants will be categorized as more stimulable (both clinicians score the participant as showing > 0% accuracy in baseline stimulability probe) or less stimulable (at least one clinician scores 0% accuracy in baseline stimulability probe). The study statistician will generate confidential participant treatment assignments in batches, where each batch corresponds to a combination of site (Montclair State University versus Syracuse University) and response category (more versus less stimulable). Within each batch, half of the participants in each of the four combinations of accuracy level and site will be allocated to the in-person condition and half allocated to the online condition. To avoid a situation where study team members can predict the allocation of an upcoming participant based on their knowledge of previous allocations within the batch, batch sizes were randomly chosen from a collection of possible sizes ranging from 16 to 96 (reflecting the fact that the size of each batch needs to be a multiple of eight).

In cases where a participant drops out prior to study completion, we will invite the participant to return for a follow-up assessment after the typical duration of treatment elapses, in order to measure their outcomes in the absence of the treatment. For participants who decline to participate in this follow-up assessment, in the intention-to-treat analysis, we will generate an imputed score based on data from the other participants in the group the missing participant was assigned to. To support this imputation, participants will complete one assessment session at the midpoint of treatment (after treatment session 10). We will also conduct an adjusted per-protocol analysis, described below under *Data analysis*.

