### Data analysis plan

The first statistical consideration for this study is the value of the margin delta (Δ), which represents the maximum acceptable loss of effect for an alternative treatment relative to an established one in a non-inferiority trial. Previous literature has suggested that delta may be defined as “less than the minimum difference of clinical interest (i.e., the minimum clinically important difference; MCID)” [28, 57]. We defined the MCID with reference to a meta-analysis of eleven single-case experimental studies of biofeedback intervention for RSSD previously published by our team [58]. In this meta-analysis, we generated de-identified plots of participants’ accuracy before and after treatment, based on perceptual ratings aggregated over blinded listeners. Three experienced researchers visually inspected these plots and reached a consensus judgment classifying each participant as responding or failing to respond to treatment. This “gold standard” binary classification was then used to compute sensitivity, specificity, and combined sensitivity-specificity for various cutoff values. ROC curve analysis revealed that a raw mean difference of 13.9% points represented the optimal cutoff between responder and non-responder categories (optimal combined sensitivity-specificity using Youden’s J). We adopt this cutoff value as the MCID. However, it is recommended that Δ be set to a value less than the MCID. Previous non-inferiority trials in the speech context have considered different values, including half of the MCID [27] or 75% of the MCID [28]. Based on the argument that high variability in response to speech treatment may lead to large confidence intervals [28], we will set our value of delta to 75% of the MCID, or 10.4% points.

The primary statistical model described below will be fit twice, once following the intention-to-treat principle, with imputed scores generated for cases of attrition, and once in an adjusted per-protocol analysis; see below for additional detail. Assessment of outcomes following both approaches is recommended for non-inferiority trials [25]. If the lower bound of the 95% confidence interval centered on the observed difference falls above the noninferiority margin of -10.4 in both models, we will conclude that noninferiority has been established.

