In the intention-to-treat analysis, we will impute an outcome for participants who drop out of the study and are lost to follow-up based on data from the individuals who have complete data and are in the same treatment assignment. In the per-protocol analysis, we will attempt to estimate the effect of telehealth versus in-person treatment only for those in the sample who remained in the trial and completed all assessments. Because estimates of this effect can be biased due to systematic differences that arise when focusing on this non-random sample from the trial, we will perform an *adjusted* per-protocol analysis using inverse probability of treatment weighting, following recommendations from recent methodological research [59, 60].

Our primary outcome measure of interest is change in perceptually rated accuracy of /ɹ/ sounds from pre- to post-treatment, with perceptual ratings of pre- and post-treatment probes obtained from blinded listeners as described above. We will compute this change score for all participants and will use a linear model with a fixed effect of group to compute the 95% confidence interval around the difference in change scores between groups. The in-person group will be treated as the reference level, so that a negative value indicates smaller gains when treatment is delivered via telepractice versus in-person. The model will also control for the randomization strata of site and baseline severity group (less stimulable versus more stimulable), as well as baseline accuracy as a continuous predictor. Lastly, we do not plan to include a fixed effect of age because our previous research has not supported such an effect (e.g [61]). However, we will test for a correlation between age and treatment outcomes and if a statistically significant correlation is present, we will include age as a controlled covariate.

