A second limitation of the non-inferiority design is the potential for non-adherence to the proposed treatment package to influence the conclusions of the study. In our research, the most common form of non-adherence is early study termination. If the types of study participants who terminate early in one condition are different from those that terminate early in the other, the intention-to-treat analysis might provide an overly optimistic assessment regarding non-inferiority. However, if these differences are explainable by our observed covariates, our adjusted per-protocol estimate could help remedy this situation. In accordance with recommendations for non-inferiority studies, we intend to report the results of the VISIT trial using both intention-to-treat and per-protocol analyses. For a strong conclusion of non-inferiority, both methods must show no difference between the treatment conditions exceeding the margin Δ. The US Food and Drug Administration recommends “close examination” of results where a discrepancy is observed between the intention-to-treat and per-protocol analyses. For example, consider a hypothetical scenario where the true effect size of treatment is smaller in the online condition than the in-person condition, but attrition is higher in the in-person condition, which could arise if participants find it more challenging to comply with the prescribed treatment schedule when visits are in-person. This could manifest as a difference in outcomes between the intention-to-treat analysis and the per-protocol analysis, with the latter showing a difference between treatment conditions and the former showing none. While such a finding would not support a strong conclusion of non-inferiority, it could still provide valuable information about real-world strengths and limitations of different service delivery methods. The inclusion of such results in the evidence base could help clinicians and clients make an informed decision based on their own personal values and needs.

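### Lost children are imputed from same-arm children with complete data while returning dropouts are scored off treatment, so the intention-to-treat leg mixes two estimands and leans towards the completer result

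*Protocol article*

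**What the plan says.** Two sections of the protocol article set the rule for children who stop early.

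- **Group allocation.** Every dropout is invited back once the usual treatment period has passed, "in order to measure their outcomes in the absence of the treatment". For those who decline, "we will generate an imputed score based on data from the other participants in the group the missing participant was assigned to". A midpoint assessment after session 10 is collected to support this imputation.
- **Data analysis plan.** For the intention-to-treat model, "we will impute an outcome for participants who drop out of the study and are lost to follow-up based on data from the individuals". The donor pool is limited to children "who have complete data and are in the same treatment assignment". The per-protocol model uses children who stayed in the trial and completed all assessments, with inverse probability weighting. Non-inferiority is concluded only if the lower 95% confidence limit is above -10.4 in both models.

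Potential limitations explains what the two models are expected to reveal. If telepractice is truly worse and in-person attrition is higher, the two analyses could differ, "with the latter showing a difference between treatment conditions and the former showing none", where the latter is the per-protocol analysis.

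**The concern.** The same event, stopping treatment early, receives two meanings in one estimate. A child who stops and returns contributes an off-treatment outcome. A child who stops and stays away contributes an outcome modelled on children with complete data, most of whom finished. The first is a treatment-policy question. The second asks what would have happened had the child finished.

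Filling gaps from same-arm completers also pulls the intention-to-treat difference towards the completer difference, and the per-protocol model rests on those completers too. The contrast described under Potential limitations would then come mainly from the dropouts who return. If telepractice loses more children and they do worse than finishers, both legs can err towards non-inferiority together.

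Separately, both sections speak of one score or outcome per lost child and mention no variance correction. If one value is filled in and analysed as observed, the intention-to-treat interval is too narrow.

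**Working it through.** **Inputs from the protocol article.** Sample size: "the sample size of 38 participants per group was computed to achieve 80% power for an alpha level of 5" per cent. SD: "after controlling for effects of clinician and baseline accuracy, was estimated at 18% points". Margin: "we will set our value of delta to 75% of the MCID, or 10.4% points" (0.75 × 13.9 = 10.425). In-person mean gain in the earlier study: 39.8 points. **Assumed, because not stated:** attrition rates, the share of gain that dropouts keep, the share who return, and a midpoint-to-final correlation of 0.7.

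**The plan's own figure.** n per group = 2 × 18² × (1.645 + 0.842)² / 10.4² = 37.04, rounded up to 38. This reproduces at one-sided 5%. The decision rule uses a 95% interval, so the nominal one-sided error for the checks below is 2.5%.

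**Step 1: interval width under random loss.** If a fraction d of each arm is filled with the arm mean and treated as observed, the model SE is about (1 − d) times the true SE. The one-sided error is then Φ(−1.96 × (1 − d)):

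| Loss d | SE ratio | Error, intention-to-treat leg alone |
|---|---|---|
| 5% | 0.95 | 3.1% |
| 10% | 0.90 | 3.9% |
| 20% | 0.80 | 5.8% |
| 30% | 0.70 | 8.5% |

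A single random draw from completers gives 5.2% at 20% loss. A single regression prediction from the midpoint score gives about 4% in simulation. Across methods and simulations the range at 20% is about 4–6.6%. The joint error of both legs in the same setting is 2.0–2.6%, because the per-protocol leg must pass too.

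**Step 2: bias when lost children keep only part of the gain.** Let a be attrition and k the share of gain kept. The arm's treatment-policy gain is its completer gain × [1 − a(1 − k)]. Take a = 5% in-person, 20% telepractice, k = 0.5 and no returners, and set the treatment-policy difference at −10.4:

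- In-person: 39.8 × (1 − 0.025) = 38.81.
- Telepractice must be 38.81 − 10.40 = 28.41, so its completer gain is 28.41 / 0.90 = 31.56.
- Completer difference: 31.56 − 39.8 = −8.24. This misses the true difference by 2.16 points, about a fifth of the margin.
- Completer SE: 18 × √(1/36.1 + 1/30.4) = 4.43. The chance that an unweighted completer analysis passes is about Φ(2.16/4.43 − 1.96) = 7%.

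In simulation both legs averaged about −8.3 under these assumptions.

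**Step 3: joint pass rate with the true difference at the margin, half the gain kept** (simulated, per-protocol leg unweighted in most runs; nominal 2.5%):

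| Attrition in-person / telepractice | Returners | Both legs pass |
|---|---|---|
| 5% / 20% | none | about 6–7% |
| 5% / 20% | half | about 3–5% |
| 5% / 10% | half | 2.0–2.8% |
| 10% / 10% | none | 1.5–1.8% |
| 20% / 5% | none | 0.3–0.4% |

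The last two rows follow from the formula in Step 2. The completer difference is then −10.95 and −13.73, both further from zero than −10.4.

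**Step 4: effect of the midpoint score.** With 20% loss, where telepractice loss is driven by a poor midpoint score, unweighted completers are biased by +2.6 points and midpoint-based imputation by about 0. Joint error is 8.1% with arm-mean imputation and 4.2% with midpoint regression. Multiple imputation with the midpoint score gives an intention-to-treat error of 2.4–2.6% when loss is random or midpoint-driven. It leaves 4.0% and 6.8% at 10% and 20% loss when loss depends on the unseen final outcome.

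**The case against.** The strongest defence has five parts.

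- **Single imputation is inferred.** The singular wording may simply be per child, and the number of imputations and the variance rule commonly sit in an analysis plan that is not shown. This stands, so the narrow-interval point is conditional.
- **A reader might infer that the intention-to-treat analysis copies the completer estimate.** The documents do not support that. The copy is exact only for arm-mean imputation with no returners. A midpoint score is collected for the imputation, returning dropouts are measured, and the per-protocol leg is weighted. The midpoint score has limits, however. Children who leave before session 10 have none, and its relation to the final score in completers includes gains from sessions 11–20 that dropouts did not receive.
- **The donor pool may include returners.** Complete data could cover a child who stopped treatment but attended the final assessment. That is possible, but unless the imputation separates them, finishers would still dominate.
- **A reader might infer that the narrow interval inflates false claims.** Step 1 shows otherwise under random loss. It makes the intention-to-treat leg easier to pass, so the per-protocol leg decides.
- **The weakness is disclosed.** Potential limitations concedes that the intention-to-treat result may be too optimistic and offers the weighted per-protocol estimate where observed covariates explain the difference. Weighting can remove covariate-linked bias, but it does not restore the off-treatment loss among children who never return. The attrition pattern illustrated there, higher in-person, is also the one in which the rule is conservative.

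**Conclusion.** The point holds in a limited form. The text itself fixes two treatments of the same event, so the intention-to-treat estimate mixes estimands and tends towards the completer difference.

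The excess risk of a false claim needs both higher telepractice attrition and lost children doing worse than finishers. Under the assumed 5%/20% attrition with half the gain kept, the joint error is about 6–7% with no returners and about 3–5% if half return, against 2.5%. It is not inflated at equal 10% attrition and is well below nominal if in-person attrition is the higher. These figures rest on assumed attrition, gain kept, return rate and midpoint correlation, and mostly on an unweighted per-protocol model.

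It would go too far to say that requiring both models gives little protection in general. That holds fully only for arm-mean imputation without returners. This is a cheap improvement to the stated rule and does not show that the design fails.

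**What to change.** In Group allocation and Data analysis plan:

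1. Specify multiple imputation within arm, combined by Rubin's rules, using midpoint score, baseline accuracy, stimulability group, site and number of sessions attended.
2. State that lost children are treated as off treatment, consistently with returning dropouts, borrowing from same-arm returners where there are enough of them.
3. Add a tipping-point analysis that lowers imputed telepractice scores by up to 10.4 points, reported beside the primary result and not as a further success criterion.

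The assessment data needed are already planned. The cost is a somewhat wider intention-to-treat interval and some programming.

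Making the penalty a success criterion would cost power. With 38 per group the SE is 18 × √(2/38) = 4.13, and power at a true difference of zero is Φ(10.4/4.13 − 1.96), about 71%. If 20% of telepractice scores were lowered by the full 10.4, the shift would be 2.08 points and power Φ(8.32/4.13 − 1.96), about 52%, before any loss of precision.

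### The adjusted per-protocol analysis weights for treatment, which is randomised, although the bias it targets comes from who completes; dropout related to response during treatment is left uncorrected

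*Protocol article*

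**What the plan says.** Under Data analysis plan, the per-protocol analysis estimates the effect "only for those in the sample who remained in the trial and completed all assessments". The same paragraph warns that such estimates can be "biased due to systematic differences that arise when focusing on this non-random sample from the trial", and the remedy it names is an adjusted "per-protocol analysis using inverse probability of treatment weighting, following recommendations from recent methodological research". It does not say which children the weight model is fitted to or which covariates enter it.

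Four other statements bear on this:

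- **Allocation** (Group allocation): "Participants will be randomly allocated to one of two groups in a 1:1 ratio".
- **Non-adherence** (Potential limitations): in the team's research "the most common form of non-adherence is early study termination".
- **Outcome model** (Data analysis plan): "The model will also control for the randomization strata of site and baseline severity group", and for baseline accuracy as a continuous predictor.
- **Midpoint visit** (Group allocation): "To support this imputation, participants will complete one assessment session at the midpoint of treatment (after treatment session 10"). No use of it in the per-protocol weights is mentioned.

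Non-inferiority is concluded only if the lower 95% confidence bound lies above -10.4 in both the intention-to-treat and the per-protocol model.

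**The concern.** The problem described and the method named do not match. The bias comes from selection on a post-randomisation event, staying to the end. The named weights model the probability of being in one arm or the other, which the design fixes at one half.

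The analysis is also the plan's safeguard. Potential limitations concedes that intention-to-treat could look too favourable if different kinds of children stop early in the two arms. It then offers the per-protocol adjustment as a possible remedy: "if these differences are explainable by our observed covariates, our adjusted per-protocol estimate could help remedy this situation". If children stop because treatment is or is not working, the natural predictor is their response so far. Ordinary treatment weights do not use that predictor, because it arises after randomisation. One of the two deciding estimates would then be called adjusted while still carrying this part of the bias.

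**Working it through.** **Inputs from the article.** Margin: 0.75 × 13.9 = 10.425, stated as 10.4. Adjusted SD 18; 38 per arm. As a check on these, 2 × 18² × (1.645 + 0.842)² / 10.4² = 37.04, rounded up to 38, which reproduces the stated sample size at one-sided 5%. The article gives no dropout rates, so every dropout figure below is an assumption.

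**Step 1: what treatment weights can do.**
- *Fitted on all randomised children:* the propensity is 0.5 by design, so all weights are about 2 and the weighted and unweighted estimates agree.
- *Fitted among completers:* the weights depend on arm and baseline covariates only. They can rebalance those covariates, but not the part of the response that is independent of baseline.

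**Step 2: size in one worked scenario.** Let r be a standard normal response during treatment, correlated 0.7 with the final score. Take a true difference of -8. The completion logit is 2.2 in person and 1.7 + 1.0r in telepractice, so dropout is about 10% and 19%.

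For p = expit(a + br), the mean of r among completers is b × E[p(1-p)] / E[p].
- Telepractice: 0.1353 / 0.8069 = 0.168. Shift in the outcome: 0.7 × 18 × 0.168 = 2.11.
- In person: b = 0, so no shift.
- Expected completer difference: -8 + 2.11 = -5.89.

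Simulation with 400,000 children, using the planned linear model:

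| Completer analysis | Estimate (truth -8) |
|---|---|
| Unweighted | -5.88 |
| Treatment weights, either fitting set | -5.88 |
| Completion weights using the midpoint score | -7.96 |

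If in-person completion also depends on response (slope 0.5), its shift is 0.7 × 18 × 0.5 × 0.0945 / 0.8913 = 0.67. The expected difference is then -8 + 2.11 - 0.67 = -6.56, again unchanged by treatment weights.

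**Step 3: direction.** With response-related dropout in the in-person arm instead, the completer estimate was -9.39 against -8, so the bias ran against telepractice. Treatment weights do not correct that either.

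**Step 4: range.** A second set of runs took a true difference of 0, in-person dropout of 10–30%, telepractice dropout of 5–10%, and half the outcome variance coming from the driver of dropout. All bias figures are in points.

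| Driver of dropout | Unweighted | Treatment weights, all randomised | Treatment weights, completers | Completion weights |
|---|---|---|---|---|
| Measured baseline variable not in the outcome model | -1.2 to -4.4 | -1.2 to -4.4 | about 0 | about 0 |
| Response during treatment | -1.2 to -4.4 | -1.2 to -4.4 | -1.2 to -4.4 | about 0 |

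Against the margin, 1.2 / 10.4 = 0.12 and 4.4 / 10.4 = 0.42.

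**Step 5: effect on the decision.** With all 76 children, SE = 18 × √(2/38) = 4.13, so a favourable bias of 2.1 is 0.51 SE. At a true difference of -10.4, the chance that this analysis passes rises from 2.5% to 1 - Φ(1.96 - 0.51), about 7%. The joint chance is lower because intention-to-treat must pass too.

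**Step 6: can completion weights be fitted at this size?** At the Step 2 rates, 38 × 0.10 is about 4 in-person dropouts and 38 × 0.19 about 7 in telepractice. Separate models by arm with five predictors had separation or no dropouts in 37% of simulated trials in person and 6% in telepractice. One small pooled, penalised model with truncated weights did work. Its mean estimate was -7.40 against -5.86 unweighted (truth -8), with root mean squared error 4.46 against 4.95.

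**The case against.** A reader might infer that the planned weighting is useless and that all the selection bias stays in. The article does not support that. Its target is the completers, and a treatment model fitted in that set is coherent: it removes selection through measured baseline variables almost entirely (Step 4). Selection through site, stimulability group and baseline accuracy is handled by the linear model in any case.

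A reader might also infer that the bias favours telepractice. The article does not settle the direction, and its own hypothetical has more attrition in person. The scenario in Step 2 was chosen to isolate response-driven dropout, so it says nothing about how common such dropout will be.

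The word treatment may be shorthand for staying on treatment, and the two methods references are not at hand. If so, the published name is wrong for an analysis that helps decide the trial, and still needs correcting.

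The article is also candid that the adjustment depends on observed covariates. It invites children who drop out back for assessment, and it requires intention-to-treat to pass as well. These points limit the damage. They do not bring information on response into the per-protocol weights, and the follow-up of dropouts serves the intention-to-treat analysis.

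Finally, a rich completion model cannot be fitted reliably with a handful of dropouts per arm. That objection stands and shapes the fix.

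**Conclusion.** The point holds in a limited form. The named weights do not address the selection the article describes. They do nothing if fitted on all randomised children, and if fitted among completers they add only balance on baseline variables beyond those already modelled. On either fitting, dropout related to response during treatment is uncorrected.

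The remaining bias is illustratively 1 to 4 points of a 10.4-point margin, in either direction. That range rests on assumed dropout rates, on assumed strength of the link between response and dropout, and on normal outcomes with SD 18. If dropout is rare or unrelated to response, the bias is negligible. The method should be changed because the analysis is co-decisive and a better-matched one is available from data already planned.

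A reader might go further and ask for the per-protocol set to be redefined by delivery mode received. Nothing in the article points to switching of mode, so that is optional and not part of this conclusion.

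**What to change.** Replace the treatment weights with inverse-probability-of-completion weights, and pre-specify:

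- **One small model pooled over arms:** arm, baseline accuracy, midpoint score and arm-by-midpoint, penalised if dropouts are few.
- **Sessions attended left out:** early stoppers attend fewer sessions by definition, so it nearly determines completion.
- **A rule for children who stop before the midpoint visit,** who have no midpoint score.
- **Truncation of the weights at a stated limit,** with robust or bootstrap standard errors.

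If treatment weights are kept, state that they are fitted among completers, list the covariates, and say that only baseline-driven selection is addressed.

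The cost is a change of wording and one extra model; the midpoint assessment is already scheduled. The downside is somewhat variable weights, and residual bias where the midpoint score is missing or measures response imperfectly. In a run where dropout followed a response that the midpoint score captured only in part, completion weights moved the estimate from -5.53 to -7.20 against a truth of -8, and treatment weights recovered nothing.

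### Whether age is in the primary non-inferiority model depends on a significance test on the trial's own outcomes, so the confirmatory covariate set is not fixed in advance

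*Protocol article*

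**What the plan says.** All of the relevant text is in the Data analysis plan section of the protocol article.

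- **Primary model.** The analysts "will use a linear model with a fixed effect of group to compute the 95% confidence interval around the difference in change scores between groups". Besides group, "The model will also control for the randomization strata of site and baseline severity group", and baseline accuracy enters as a continuous predictor.
- **Age, default.** The authors state that "we do not plan to include a fixed effect of age because our previous research has not supported such an effect".
- **Age, exception.** They then say that "we will test for a correlation between age and treatment outcomes" and that "if a statistically significant correlation is present, we will include age as a controlled covariate".
- **Role of the model.** "The primary statistical model described below will be fit twice": once by intention to treat with imputed scores, and once as an adjusted per-protocol analysis.
- **Decision rule.** "If the lower bound of the 95% confidence interval centered on the observed difference falls above the noninferiority margin of -10.4 in both models", non-inferiority is concluded. The margin comes from the statement that "we will set our value of delta to 75% of the MCID, or 10.4% points".

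Nothing else in the article fixes the age decision or makes the age-adjusted fit a sensitivity analysis.

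**The concern.** The trial's conclusion rests on one confidence limit compared with -10.4, required in two fits of one model. Site, stimulability group and baseline accuracy are fixed covariates in that model. Age is not: its presence depends on whether a correlation estimated from the trial's outcomes crosses a significance threshold. With 76 children, that threshold falls where modest true correlations would put the estimate, so nobody can say beforehand which model will be the confirmatory one.

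Adding or removing a covariate moves both the point estimate and the standard error a little. When the lower limit is close to -10.4, that can change the verdict. A critic could then fairly say that the conclusion turned on a side test. Age is recorded for every child at enrolment (9;0 to 17;11, Eligibility criteria), so the decision need not wait for outcomes.

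**Working it through.** **Inputs from the protocol article.** 38 children per group, 76 in total. SD 18 points after controlling for clinician and baseline accuracy. Margin 0.75 × 13.9 = 10.425, stated as 10.4. Power 80%, alpha 5% (Methods and design; Data analysis plan). Allocation 1:1 (Group allocation).

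**Assumed.** The age-outcome correlation ρ, which the article does not give, is set at 0, 0.2, 0.3 and 0.5. The preliminary test is taken as two-sided at 5%, and the confidence interval as two-sided 95%.

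**Step 1. The plan's own sample size.** n per group = 2σ²(z₁₋α + z₁₋β)²/Δ² = 2 × 324 × (1.645 + 0.842)²/10.4² = 37.04, rounded up to 38. The stated figure reproduces with one-sided alpha 0.05 and a true difference of 0. With the two-sided 95% limit of the decision rule, SE = 18 × √(2/38) = 4.13, and power = Φ(10.4/4.13 − 1.96) = Φ(0.56) = 0.71. This explains why the simulated powers below lie near 0.70 rather than 0.80. It is a separate matter from the age rule.

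**Step 2. Where the test switches.** With n = 76, t₀.₉₇₅,₇₄ = 1.993. The critical correlation is 1.993/√(1.993² + 74) = 0.226. An observed 0.22 leaves age out, and 0.23 brings it in.

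**Step 3. How often age enters.** By Fisher's transformation, the chance of selection is about Φ(atanh(ρ) × √73 − 1.96).
- ρ = 0: 5%, by construction.
- ρ = 0.2: Φ(0.2027 × 8.544 − 1.96) = Φ(−0.23) = 0.41.
- ρ = 0.3: Φ(0.3095 × 8.544 − 1.96) = Φ(0.68) = 0.75.

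Simulation at a true difference of 0 gave 4.9%, 41.7% and 75.9%. At a true difference of −10.4 it gave 5.0%, 38.7% and 72.2%. The latter are lower because the group difference adds 10.4²/4 = 27.0 to the outcome variance of 324 and so dilutes the raw correlation.

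**Step 4. Error and power.** 20,000 simulated trials per setting, 38 per arm, residual SD 18, with group, site, stimulability group and baseline accuracy in the model. Age is never in, always in, or in by the conditional rule.

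| ρ | One-sided error at −10.4: never / always / conditional | Power at 0: never / always / conditional |
|---|---|---|
| 0 | 0.0242 / 0.0242 / 0.0249 | 0.682 / 0.675 / 0.682 |
| 0.2 | 0.0240 / 0.0240 / 0.0248 | 0.682 / 0.693 / 0.695 |
| 0.3 | 0.0251 / 0.0266 / 0.0274 | 0.680 / 0.713 / 0.712 |
| 0.5 | 0.0254 / 0.0244 / 0.0244 | 0.679 / 0.794 / 0.794 |

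The simulation standard error on each error rate is √(0.025 × 0.975/20,000) = 0.0011. A separate 40,000-run simulation with all planned covariates gave coverage of 0.950 to 0.952 and one-sided error of 0.024 to 0.026 under the conditional rule. Always versus conditional power in that run was 0.686/0.693, 0.702/0.703 and 0.728/0.727 at ρ = 0, 0.2 and 0.3. The largest gap is 0.7 points in favour of the conditional rule, at ρ = 0.

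**Step 5. How often the verdict depends on the choice.** At a true difference of 0, the models with and without age disagree on non-inferiority in 2.8%, 5.9%, 9.1% and 16.5% of trials at ρ = 0, 0.2, 0.3 and 0.5. The conditional rule and the always-adjusted model disagree less often: 2.3%, 2.2% and 1.0% at ρ = 0, 0.2 and 0.3 (200,000 runs, group and age only), or about 1 to 2.5% overall.

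**The case against.** The strongest defence is that the rule is itself written in advance. It names one covariate, a default, a trigger and a consequence. The trigger is the age-outcome correlation, not the group difference or the confidence limit. That stands as far as it goes: this is not a free choice made after seeing the treatment effect, and a reader who inferred that would be going beyond the text. But a fixed rule is not a fixed model, and the decision rule needs the model.

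Three stronger readings are tempting, and none is supported.

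- **Lost coverage or inflated error.** A reader might expect a model chosen from the data to give an invalid interval. Allocation is randomised, so age is unrelated to group in expectation, and Step 4 shows coverage and error essentially at nominal.
- **A power gain from always adjusting.** Going from never to always adjusting at ρ = 0.3 raises simulated power from 0.680 to 0.713. Never adjusting is not the protocol's rule, however. Against the conditional rule the gain is nil, and at ρ = 0 always adjusting loses about 0.7 points.
- **Different covariates in the two fits.** If the test were run separately in each analysis set, with an assumed 10% random dropout, the sets would select different models in about 3%, 11% and 9% of 6,000 simulated trials at ρ = 0, 0.2 and 0.3. The article does not say that the test is repeated, and "The primary statistical model described below will be fit twice" reads more naturally as one model.

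The level of the test and the outcome and analysis set it uses are details that an analysis plan may give. Their absence from the article is not counted here. The authors' reason for leaving age out is legitimate too, and it supports a fixed exclusion as well as any argument supports a fixed inclusion.

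**Conclusion.** The point holds as one of model specification. The protocol article states a rule under which the confirmatory covariate set is known only after outcomes have been examined. At modest correlations, which of the two models results is hard to predict: age enters in about 40% of trials at 0.2 and 75% at 0.3. The practical effect is small and sits near the margin, with a different non-inferiority conclusion from the always-adjusted model in about 1 to 2.5% of trials at a true difference of 0. It is not a problem of error inflation or lost power. The rule also brings no material power benefit to set against the ambiguity.

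These sizes rest on assumed correlations, a residual SD of 18, normal errors, complete data on 76 children and a two-sided 5% preliminary test. That the model is left undetermined follows from the text alone.

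**What to change.** Delete the preliminary correlation test and state the age decision now, before any outcome data are analysed, in the same form for the intention-to-treat and adjusted per-protocol fits.

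- **Preferred:** include age at enrolment as a linear covariate in both fits, whatever its observed correlation with outcome. This costs one sentence, one degree of freedom and under 1 point of power if age is not prognostic.
- **Alternative:** keep age out of both fits, in line with the authors' stated rationale, and report the age-adjusted fit as a sensitivity analysis that does not enter the non-inferiority decision.

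Either choice removes the defect and leaves the stated 38 per group unchanged.
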